## **6.5. Indications for withdrawal of treatment**

Treatment should continue until child-birth unless:

- A known serious adverse reaction to pravastatin occurs
- A suspected unexpected serious adverse reaction occurs
- Child-birth of the baby is imminent, according to criteria given below in 6.5.1
- The mother refuses to take the trial drug

If the symptoms of pre-eclampsia progress but do not necessitate child-birth, the trial drug should continue to be taken. This is irrespective of any other medication prescribed.

If, for whatever reason, the patient discontinues treatment, she will not be withdrawn from the trial and data collection will continue to allow intention to treat analysis, unless consent to do this is withdrawn. Rates will be monitored to detect differential drop-out, which can bias clinical trial results and reduce the power of the trial to detect important differences.

### **6.5.1. Time of child-birth**

Indications for child-birth is a clinical decision, which to some extent will vary between clinicians at different centres. Investigators from all participating centres have agreed that maternal indications for child-birth include uncontrollable severe hypertension (BP $\geq$ 170/110mmHg), elevated liver transaminases >500IU/L, elevated SCr >120 $\mu$ mol/L, thrombocytopaemia <50,000 or eclampsia. Fetal indications include non-reassuring CTG or worse, or reversed end diastolic flow (EDF). Lesser maternal signs may warrant child-birth if combined or if accelerating rapidly. The time that the decision was made to deliver the baby should be recorded.

## **6.6. Sample collection**

### **6.6.1. Blood sample collection**

Blood samples of 5-10mls will be collected for the analysis of inflammatory and anti-angiogenic factors including s-Flt-1, PlGF, and sENG. As a minimum, samples need to be collected daily at baseline, on days 1-3 of the trial treatment period and twice a week thereafter until discharge from hospital post-delivery. Blood samples should be taken at the same time as routine sampling wherever possible, however where this is not possible, additional samples may occasionally need to be taken specifically for the trial. All samples should be spun down and plasma collected. The plasma sample tube should be labelled with a pre-printed label containing StAmP Trial Number, sample day and type. Patient initials, date of birth and date of sample should be written on the label. Samples will be stored in a -80°C freezer (or -20°C if not available) within a StAmP sample storage box, until the mother has completed her involvement in the trial.

Once the mother has completed her involvement in the trial (after the 6-week post-partum blood sample collection), all tubes should be sealed and sent to Aston University as and when instructed by the StAmP Trial Office.

The StAmP Trial Office will send out instructions on sample preparation, freezing and transport guidelines to all participating centres.

#### **6.6.2. mRNA sample collection**

Two blood samples will be collected for mRNA extraction. This is in addition to the blood samples in section 6.6.1. These will be used to determine the level of heme oxygenase-1 (HO-1) expression. Blood samples should be taken at baseline and on day 3 of trial treatment period. A minimum of 2.5 ml of blood is required. The tubes should be labelled with a pre-printed label containing StAmP Trial Number, sample day and type. Patient initials, date of birth and date of sample should be written on the label. The tubes must be stored upright at room temp for over 2 hours (max 72 hours) and then stored in a -80°C freezer (or -20°C if not available) within the StAmP sample storage box.

Once the mother has completed her involvement in the trial (after the 6-week post-partum blood sample collection), all tubes should be sealed and sent to Aston University as and when instructed by the StAmP Trial Office.

The StAmP Trial Office will send out instructions on sample preparation, freezing and transport guidelines to all participating centres.

#### **6.6.3. Urine sample collection**

Three urine samples will be collected at baseline, on day 3 of trial treatment period and at delivery. These will be used for the analysis of inflammatory and anti-angiogenic factors including s-Flt-1 and PlGF. 5ml of urine is required. The tubes should be labelled with a pre-printed label containing StAmP Trial Number, sample day and type. Patient initials, date of birth and date of sample should be written on the label. The tubes must be stored in a -80°C freezer (or -20°C if not available) within the StAmP sample storage box.

Once the mother has completed her involvement in the trial (after the 6-week post-partum blood sample collection), all tubes should be sealed and sent to Aston University as and when instructed by the StAmP Trial Office.

The StAmP Trial Office will send out instructions on sample preparation, freezing and transport guidelines to all participating centres.

#### **6.6.4. Cord blood sample collection**

A blood sample will be collected from the umbilical cord at delivery from a sample of women. This will be used to measure the level of pravastatin in the blood. A minimum of 1-5ml of cord blood is required. The sample should be spun down and the plasma collected. The plasma sample tube should be labelled with a pre-printed label containing StAmP Trial Number, sample day and type. Patient initials, date of birth and date of sample should be written on the label. Samples will be stored in a -80°C freezer (or -20°C if not available) within a StAmP sample storage box, until the mother has completed her involvement in the trial.

Once the mother has completed her involvement in the trial (after the 6-week post-partum blood sample collection), all tubes should be sealed and sent to Aston University as and when instructed by the StAmP Trial Office. These will later be sent to the Institute of Child Health at University College London for analysis.

The StAmP Trial Office will send out instructions on sample preparation, freezing and transport guidelines to all participating centres.

### **6.6.5. Placenta sample collection**

Samples of placenta will be endeavoured to be collected at delivery from all women who have consented to this, however this will only be carried out at selected participating sites who have the resources and equipment to enable the placenta collection. This will be used to measure levels of inflammatory and anti-angiogenic factors including s-Flt-1 and PlGF and also the level of Pravastatin crossing to the placenta from maternal circulation.

Where possible, three 1cm^2 full thickness biopsies of placenta are needed. Each sample should be transferred into a sample tube and snap frozen in liquid nitrogen. (If liquid nitrogen is unavailable, the sample can be stored directly in a -80°C freezer). The sample tube should be labelled with a pre-printed label containing StAmP Trial Number, sample day and type. Patient initials, date of birth and date of sample should be written on the label. Samples must be stored in a -80°C freezer within a StAmP sample storage box, until the mother has completed her involvement in the trial.

Where possible, one additional sample of placenta will be collected and fixed in formalin. One 1cm^2 thickness biopsy of placenta should be placed in a universal tube and fixed for 24 hours in about 20ml of 10% neutral buffered formalin (3.7-4% formaldehyde) at room temperature. The sample should then be transferred into a 5ml cryovial containing 70% ethanol. The sample tube should be labelled with a pre-printed label containing StAmP Trial Number, sample day and type. Patient initials, date of birth and date of sample should be written on the label. Samples must be stored at 4°C, until the mother has completed her involvement in the trial.

Once the mother has completed her involvement in the trial (after the 6-week post-partum blood sample collection), all tubes should be sealed and sent to Aston University as and when instructed by the StAmP Trial Office.

The StAmP Trial Office will send out instructions on sample preparation, freezing and transport guidelines to all participating centres.

## **7. SAFETY MONITORING PROCEDURES**

There may be unexpected serious adverse reactions associated with pravastatin when used in pregnancies affected by pre-eclampsia. The clinical trials that led to the licensing of statins excluded pregnant women. The subsequent contraindication of statins in pregnancy has meant there is little experience of statin use in pregnancy. Statins used to treat hypercholesterolaemia outside pregnancy have been associated with rare but serious adverse reactions (see Appendix D). Metabolic changes during pregnancy may alter the pharmacological properties and toxicity of pravastatin in unanticipated ways.

The Medicines for Human Use (Clinical Trials) Regulations 2004 define categories of adverse events, the responsibilities of the investigators to notify adverse events to the sponsor and for the sponsor to report to the regulatory authority and ethics committee. It is therefore imperative that all investigators have a thorough understanding of anticipated adverse events and the reporting process of these events.

### **7.1. General Definitions**

#### **Adverse Events (AEs)**

An AE is:

- any unintentional, unfavourable clinical sign or symptom. This will include complications of pre-eclampsia.
- any new illness or disease or the deterioration of existing disease or illness

- any clinically relevant deterioration in any laboratory assessments or clinical tests

The following are not AEs:

- A pre-existing condition (unless it worsens significantly during treatment).
- Diagnostic and therapeutic procedures, such as surgery (although the medical condition for which the procedure was performed must be reported if new)

### **Adverse Reactions (ARs)**

An AR is an adverse event that is considered to have a “reasonable causal relationship” with trial drug.

### **Serious Adverse Events (SAEs)**

An SAE is an untoward event which:

- Results in maternal or fetal death
- Immediately threatens the life of mother or baby\*
- Results in a longer than anticipated post-natal maternal stay in hospital
- Results in a persistent or significant disability in the mother
- Results in any congenital anomaly or birth defect in the baby, once delivered, that had not been identified by antenatal ultrasound prior to the onset of pre-eclampsia

\*Life-threatening in the definition of a serious adverse event or serious adverse reaction refers to an event in which the subject was at risk of death at the time of the event. It does not refer to an event which hypothetically might have caused death if it were more severe. Important adverse events/reactions that are not immediately life-threatening or do not result in death or hospitalisation, but may jeopardise the subject or may require intervention to prevent one of the other outcomes listed in the definition above, should also be considered serious.

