### **Events NOT considered to be SAEs are hospitalisations for:**

- routine treatment or monitoring of pre-eclampsia, not associated with any deterioration in condition
- treatment, which was elective or pre-planned, for a pre-existing condition that is unrelated to the indication under study, and did not worsen
- admission to a hospital or other institution for general care, not associated with any deterioration in condition
- treatment on an emergency, outpatient basis for an event not fulfilling any of the definitions of serious given above and not resulting in hospital admission

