### 8.2. Secondary outcome measures

Secondary measures will be:

- The level of maternal circulating sFlt-1 and the ratio of sFlt-1 to PlGF over the first 14 days post-randomisation. Most women are expected to provide regular measurements before childbirth. Pregnancy with pre-eclampsia is expected to last for an average  $11\pm 5$  days, so estimates of effects over the first two weeks are expected to be from a largely complete set of data. All available data, both clinical and biochemical will be examined to see if this influences interpretation of results.
- Severity of pre-eclampsia as indicated by maternal blood pressure, level of proteinuria, platelet count, liver-transaminases, renal function, fetal biometry and umbilical artery blood flow 48 hours after randomisation and for the remainder of the pregnancy.
- Length of gestation post-randomisation, in days.
- Maternal morbidity, as indicated by serum creatinine  $\geq 120\mu\text{mol/L}$ , proteinuria  $\geq 5\text{g/24h}$ ; signs of left ventricular failure (pulmonary oedema, oxygen sats  $< 95\%$ ); hypertension  $\geq 170/110\text{mmHg}$  despite anti-hypertensive treatment; disseminated intravascular coagulation and/or platelets  $< 50 \times 10^9$ ; eclampsia; cerebrovascular event; liver transaminase  $\geq 500\text{IU/L}$ , more than 48 hours after randomisation and for the remainder of the pregnancy.
- Neonatal Apgar score at 1, 5, 10 minutes
- Use of anti-hypertensives
- Level of pravastatin in the cord blood at delivery relative to maternal levels.
- Serious adverse events and reactions

Secondary outcomes will be collected prior to randomisation, daily throughout pregnancy and at birth. The data items collected to identify secondary outcomes are shown in Table 1.

When analyzing secondary outcomes, length of gestation post randomization will be considered the most important indicator of potential clinical efficacy.

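### Section 7.1 contradicts itself on whether hospital admission makes an event serious, so some post-natal maternal readmissions can be classed either way.

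*Combined protocol and SAP*

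**What the plan says.** Section 7.1 of the protocol defines an SAE by five criteria: death of mother or fetus, immediate threat to the life of either, a prolonged post-natal stay, lasting or significant disability in the mother, and a congenital anomaly not identified on ultrasound before the disease began. The third is the only one about hospital use: "Results in a longer than anticipated post-natal maternal stay in hospital".

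A footnote adds a catch-all. It begins "Important adverse events/reactions that are not immediately life-threatening or do not result in death or hospitalisation" and ends by saying that such events, if they "may jeopardise the subject or may require intervention to prevent one of the other outcomes listed in the definition above, should also be considered serious".

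The next subsection is headed "Events NOT considered to be SAEs are hospitalisations for". It exempts routine treatment or monitoring of pre-eclampsia and general-care admission, in each case without deterioration. It also exempts "treatment, which was elective or pre-planned, for a pre-existing condition that is unrelated to the indication under study, and did not worsen" and "treatment on an emergency, outpatient basis for an event not fulfilling any of the definitions of serious given above and not resulting in hospital admission".

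Adverse events are collected from the first dose until six weeks after child-birth (section 7.2). The local Principal Investigator or another nominated clinician assigns seriousness (sections 7.3 and 7.6). Section 8.2 lists "Serious adverse events and reactions" among the secondary outcomes.

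**The concern.** The criteria list and the text around it give different answers to a plain question: is a woman who goes home after the birth and is then readmitted unexpectedly an SAE? The list does not say that she is. The footnote and the exemptions assume that she is, unless an exemption applies.

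Seriousness decides what happens next. An SAE needs a form within 24 hours (section 7.3), goes to the DMEC about every three months (sections 7.3 and 7.6), is reviewed by the Chief Investigator (section 7.6), can become a SUSAR (sections 7.1 and 7.4) and counts towards a secondary outcome (section 8.2). A non-serious event has no expedited report (section 7.2). Section 7 itself warns that pregnancy may change the drug's toxicity in ways that cannot be foreseen, so complete capture of serious events matters here.

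**Working it through.** There is no figure in the plan to reproduce. The check compares the texts.

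**1. The criteria list alone.** Of the five criteria, 0 name an admission or readmission, and 1 concerns a prolonged post-natal stay. On its natural meaning, that one covers a stay that runs on, not a new admission after discharge.

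**2. The footnote.** It describes a residual class of important events and names hospitalisation beside death and threat to life as outcomes outside that class. This treats hospitalisation as already listed. It is not.

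**3. The exemptions.** Excusing planned treatment, and admissions without deterioration, serves a purpose only if other admissions count. The last exemption uses admission directly as a test: emergency outpatient care is excused if it does not lead to one.

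**4. Where the readings part.** All women are to be inpatients until child-birth (section 8.3), so the gap bears mainly on readmission after post-natal discharge and within the six-week window:

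- Life-threatening or disabling readmission: an SAE on either reading.
- Readmission that meets an exemption, such as monitoring without deterioration: an SAE on neither.
- Unplanned readmission that is not life-threatening, not disabling and not exempt: not an SAE by the list, but an SAE by implication of the footnote and exemptions. Readmission for worsening hypertension without immediate threat to life is an example.

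**5. Whether anything else settles the third case.** The footnote's clause on events that "do not result in death or hospitalisation, but may jeopardise the subject" can make such a readmission serious, but only if the investigator judges it so. The clause's other limb concerns intervention to prevent a listed outcome, and admission is not listed. The Chief Investigator's SAE review covers events that the local investigator has already assessed as SAEs (section 7.6), so it would not pick up a readmission classed locally as non-serious. No other section answers the question.

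**6. Size.** The documents give no readmission rate. Purely as an assumption, 3% to 10% of the maximum of 64 women (section 9.1) would be 64 × 0.03 = 1.9 to 64 × 0.10 = 6.4 women. These are upper bounds for the assumed rates, because they count every readmission and only those in the third case are ambiguous. With 32 women per arm, one reclassified woman moves an arm's proportion by 1/32 = 3.1 percentage points. That would hold for any event in a trial of this size.

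**The case against.** The best defence is that the section, read as a whole, points one way. The footnote and exemptions sit next to the criteria and both imply that hospitalisation counts, and the catch-all lets an investigator report an important readmission whatever the list says. This stands in part: some readmissions are already serious under the catch-all. But that route depends on local judgement, and the list that an investigator would apply still omits admission.

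Four stronger readings are tempting, and the documents do not support them.

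- *Every unplanned readmission is ambiguous.* It is not. Life-threatening or disabling ones are SAEs on both readings, and exempt ones on neither.
- *Sites do classify differently, or the arms are biased.* Nothing shows that sites differ; they can. Seriousness is assigned blind to allocation (sections 6.4 and 7.3), so no bias between arms follows.
- *Muscle or liver reactions listed in Appendix D would be lost as SUSARs.* Section 7.1 makes SmPC-listed events expected, so they become SUSARs only through their severity. The SUSAR gap concerns unexpected suspected reactions. Treatment also stops when the pregnancy ends (section 6.2.2), so these readmissions occur off drug.
- *The DMEC would never see the event.* All AEs are recorded to six weeks, Table 1 collects maternal morbidity at six weeks, and the DMEC receives quarterly adverse-event analyses (section 9.2.2) and morbidity data (section 10.3). The event would be missing from the SAE report and the SAE outcome, not from all oversight.

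Leaving out antenatal admission may also be deliberate, because every participant is an inpatient before the birth.

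**Conclusion.** The contradiction is real and should be removed. It is a rule that gives two answers, not merely a missing detail. It is confined to unplanned maternal readmissions after post-natal discharge and within six weeks of child-birth that are not life-threatening, not disabling, not exempt, and not judged serious under the footnote's clause. Classed as non-serious, such an event misses the 24-hour report, the Chief Investigator's SAE review and the SAE secondary outcome, and any SUSAR assessment if it is an unexpected suspected reaction.

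The conclusion rests on the wording of section 7.1 and on no assumed rate. How many women are affected cannot be derived from the documents. The primary outcome, sample size and power are untouched, and section 2.4.1 says that the trial is not powered for clinical outcomes. The weight of the point is in safety capture and a consistent SAE count.

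**What to change.** Reconcile the two parts of section 7.1 by adding one criterion to the SAE list: *Results in unplanned hospital admission or readmission of the mother after post-natal discharge*. Keep the existing post-natal-stay criterion and the list of exempt hospitalisations unchanged.

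Do not extend the new criterion to antenatal or neonatal stays. A longer antenatal stay goes with a longer pregnancy, which is the hoped-for benefit, and long neonatal stays are to be expected after preterm birth. General wording about prolonging any existing stay would draw in both.

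Use this one definition on the SAE form, in the DMEC report and for the SAE outcome. The cost is one line in the protocol and on the form, and a few more SAE forms for sites to complete. No visits, samples or participants are added.

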### **Expected SAEs**

Expected SAEs are those listed in the current Summary of Product Characteristics (SmPC) for Pravastatin. These events do not meet the criteria of SUSAR unless for reason of their severity. For convenience, the

current expected events for Pravastatin are listed in Appendix D. We will however always use the most recently updated Summary of Product Characteristics (SmPC). The BCTU will ensure that any SmPC updates are circulated to all investigators; in addition, up-to-date SmPCs of licensed products are available at <http://emc.medicines.org.uk/>.

Expected SAEs also include, but are not limited to, the following:

- Symptoms and recognised complications of pre-eclampsia. These include exacerbation of hypertension, abnormal renal function, abnormal hepatic function, disseminated intravascular coagulation, cerebrovascular event, eclampsia, left ventricular failure, haemorrhage and pulmonary oedema.
- Symptoms and recognised complications of premature birth. These include seizures, necrotising enterocolitis (NEC), hypoglycaemia, jaundice, bleeding from umbilicus, and congenital anomalies.

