#### **7.5. Notification of deaths**

All deaths will be reported to the BCTU on the SAE Form irrespective of whether the death is related to disease progression, the IMP, or an unrelated event. If a mother or baby dies, any post-mortem findings must be provided to the BCTU with the SAE form. The BCTU will report all deaths to the DMEC for continuous safety review.

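### The SAE definition limits disability to the mother and names only maternal or fetal death, so whether a disabling but not life-threatening neonatal injury is an SAE rests on each centre's judgement

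*Combined protocol and SAP*

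**What the plan says.** Section 7.1 of the protocol lists five seriousness criteria:

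- Death: "Results in maternal or fetal death".
- Threat to life: "Immediately threatens the life of mother or baby".
- Hospital stay: "Results in a longer than anticipated post-natal maternal stay in hospital".
- Disability: "Results in a persistent or significant disability in the mother".
- Anomaly: "Results in any congenital anomaly or birth defect in the baby, once delivered", if it had not been seen on antenatal ultrasound before the onset of pre-eclampsia.

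A note to the second criterion adds that important events which "may jeopardise the subject or may require intervention to prevent one of the other outcomes listed in the definition above, should also be considered serious".

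Other parts of Section 7 extend to the newborn. The Expected SAEs list includes "Symptoms and recognised complications of premature birth. These include seizures, necrotising enterocolitis (NEC), hypoglycaemia, jaundice". Section 7.5 requires every death to be sent in on an SAE form and adds: "If a mother or baby dies, any post-mortem findings must be provided to the BCTU with the SAE form". Sections 7.3 and 7.5 send all deaths to the DMEC. Section 7.2 sets the adverse event window from the first dose to 6 weeks after birth.

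**The concern.** Section 2.5 makes harm to the mother or the baby the trial's second question, and Section 2.3.4 concedes that no human study gives firm reassurance about statins in pregnancy. The baby is exposed to whatever drug crosses the placenta. A disability criterion confined to the mother is narrower than that question.

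SAE status decides what happens next. It triggers reporting to the trials unit within 24 hours (Section 7.3) and inclusion in the 3-monthly SAE reports to the DMEC (Sections 7.3 and 7.6). It is also a precondition for a SUSAR, which goes to the MHRA and the ethics committee within 7 or 15 days (Section 7.4). A suspected drug-related injury to the baby that a centre judges non-serious would take none of these routes. SAEs and reactions are also a listed secondary outcome in Section 8.2. In that list the Apgar score is the only other clinical measure specific to the newborn; neonatal mortality and morbidity appear in Table 1 but not in the list.

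**Working it through.** No arithmetic applies beyond a count, and the plan states no figure to reproduce. The check compares the provisions with one another.

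**Step 1. Whom each criterion in Section 7.1 names**

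| Criterion | Mother | Fetus or baby |
|---|---|---|
| Death | Yes | Fetus only |
| Immediate threat to life | Yes | Baby |
| Longer stay | Yes | Not named |
| Lasting disability | Yes | Not named |
| Congenital anomaly | n/a | Baby |

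Two of the five name the baby, one stops at the fetus, and two are maternal only (2 + 1 + 2 = 5).

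**Step 2. Neonatal events run through all of Section 7**

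- *Baby dies after birth.* Not named under death in 7.1, but 7.5 requires the SAE form and 7.3 and 7.5 require notice to the DMEC. Captured.
- *Life-threatening neonatal event.* Captured by 7.1. The note judges risk when the event occurs, so later recovery does not remove SAE status.
- *Congenital anomaly not seen on earlier ultrasound.* Captured by 7.1.
- *Injury causing lasting disability, never immediately life-threatening, not an anomaly.* No listed criterion applies. Only the general clause can bring it in.
- *Jaundice or hypoglycaemia that does not threaten life.* Named under Expected SAEs, yet no listed criterion in 7.1 makes it serious. Again only the general clause can do so.

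**Step 3. Does the general clause settle the last two cases?** It has two limbs. The first covers events that may jeopardise the subject. The second covers events needing intervention to prevent a listed outcome. Because disability is listed for the mother only, the second limb does not reach an intervention made to prevent disability in the baby. The first limb can reach the baby: the note explains the criterion on threat to mother or baby by speaking of the subject at risk of death, so in that place the subject must include the baby. But the limb requires a judgement that the event is important, and the protocol never defines the term. Section 7.6 speaks of subjects taking part in the trial, which a centre could read as the women alone.

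**Step 4. What is recorded regardless of SAE status.** Table 1 collects neonatal mortality and morbidity at birth, until discharge and at 6 weeks, and the length of perinatal stay until discharge. Section 7.2 records all adverse events in the same period.

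**The case against.** The strongest reply is that Section 7, read as a whole, plainly intends neonatal events to be reportable. The Expected SAEs list names several, Section 7.5 captures every death, and the general clause can reach a seriously injured newborn. The DMEC also reviews overall safety and morbidity data (Sections 7.6 and 10.3), not only SAE reports. Follow-up ends at 6 weeks and infant development is declared out of scope (Section 8.5), so lasting disability could seldom be established in time. Women enter at 24+0 to 31+6 weeks, so long stays by preterm babies are foreseeable; leaving the baby's stay out of the criteria and recording it as data is a defensible choice.

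Most of this stands, and it rules out several stronger readings that a reader might infer:

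- *Neonatal deaths go uncounted.* Sections 7.3 and 7.5 require them to be reported. The omission from 7.1 is an inconsistency of wording.
- *The word subject excludes the baby.* The note in 7.1 uses it in a way that includes the baby. The term is undefined, not restricted.
- *Missed events would distort the comparison between arms.* The trial is double-blind, and Section 7.3 has SAEs assessed as though every woman were on pravastatin. The documents offer no reason for under-reporting in one arm.
- *The baby's prolonged stay must be made a criterion.* At these gestations that is a trade-off on which opinions can differ.

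The reply does not explain why disability stops at the mother. The argument about expected long stays does not carry over to disability, and the fact that few cases would be evident by 6 weeks is no reason to leave evident ones to local judgement.

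**Conclusion.** The point holds in a limited form. The disability criterion in Section 7.1 is narrower than the trial's safety question, and the definition does not match the Expected SAEs list or Sections 7.3 and 7.5. The effect is possible variation between centres in classifying neonatal harm, and hence in expedited and SUSAR reporting. The underlying data are not lost.

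The size cannot be put as a number. The class affected is neonatal injury that is disabling, never immediately life-threatening and not an anomaly, together with milder prematurity complications whose status is unclear. The documents give no rate for either. With up to 64 participants carrying singleton pregnancies, there are at most 64 babies, so the number of affected events is likely to be small. The conclusion assumes that centres work from the protocol text and receive no separate guidance that settles the matter. It is an inexpensive improvement to a rule that is drawn too narrowly.

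**What to change.** In Section 7.1:

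1. Extend the disability criterion to the mother or baby.
2. Reword the death criterion to cover maternal, fetal or neonatal death, in line with Section 7.5.
3. State that the subject includes the baby up to 6 weeks after birth, matching the window in Section 7.2.
4. Reconcile the definition with the neonatal events under Expected SAEs, by saying when a complication of prematurity counts as serious and when it is recorded only as an adverse event or as Table 1 data.

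Whether the baby's length of stay should also be a criterion can be left to the investigators; if it stays out, one sentence saying that this is intended would prevent doubt.

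The cost is a wording amendment, a matching change to the SAE form and a note to centres. The downside is slightly more SAE reports. No new data collection is needed, since Table 1 already covers neonatal morbidity.
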